**Appendix 1**

**Research Treatment Chart**

**
[figure not shown]
**

**Appendix 2**

Table 1 SPIRIT schedule

| Research Phase  Project Name | Before Treatment | First Week Treatment | Second Week Treatment | Third Week Treatment | Fourth Week Treatment | 8 Weeks After Treatment |
| --- | --- | --- | --- | --- | --- | --- |
|  | t0 | t1(5days) | t2(5days) | t3(5days) | t4(5days) | t5 |
| Screening for Enrollment | √ |  |  |  |  |  |
| Medical history and basic information | √ |  |  |  |  |  |
| Routine examinations | √ |  |  |  | √ |  |
| Informed Consent Form | √ |  |  |  |  |  |
| Drug treatment | √ | √ | √ | √ | √ | √ |
| Pelvic Pain Scale/NIH-CPSI Score | √ | √ | √ | √ | √ | √ |
| DASS-21Score | √ | √ | √ | √ | √ | √ |
| SF-36 Quality of Life Scale | √ | √ | √ | √ | √ | √ |
| Surface electromyography of the pelvic floor muscles | √ | √ | √ | √ | √ | √ |
| Pudendal nerve motor evoked potentials | √ | √ | √ | √ | √ | √ |
| Bilateral magnetic stimulation |  | √ | √ | √ | √ |  |
| Peripheral magnetic stimulation |  | √ | √ | √ | √ |  |
| Fake stimulus |  | √ | √ | √ | √ |  |
| Follow-up |  |  |  |  |  | √ |
| Adverse Event |  | √ | √ | √ | √ | √ |
| Analysis of missing items and non-respondents. |  |  |  |  |  | √ |

Note: Routine examinations include: complete blood count, liver function, kidney function, and electrocardiogram examination. Pelvic pain scale, Female Pelvic Pain Scoring Scale; NIH-CPSI, The National Institutes of Health Chronic Prostatitis Symptom Index (NIH-CPSI); SF-36,SF-36 scale of quality of life; t0, enrollment; t1, At the end of 5 sessions;t2,At the end of 10 sessions; t3,At the end of 15 sessions; t4,At the end of 20 sessions; t5, Follow-up visit 8 weeks after treatment ends.

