| 1. Features and Innovations of this Project  This study employs a prospective randomized controlled trial design, setting up a control group experiment. The control group will consist of CPPS patients receiving sham stimulation and those receiving peripheral magnetic stimulation, while the experimental group will consist of CPPS patients receiving dual-target magnetic stimulation. By comparing the clinical safety and efficacy indicators among the three groups of patients, the study aims to explore the therapeutic effects and safety of dual-target magnetic stimulation in CPPS patients with comorbid psychological disorders. Dual-target magnetic stimulation is derived from the author's team's years of clinical experience and in-depth understanding of various CPPS treatment methods. Currently, no relevant studies have been found in domestic and international literature regarding the use of this type of treatment for CPPS patients with comorbid psychological issues.   1. Feasibility Analysis (Department Conditions, Personnel Allocation, Case Sources, Technical Conditions, etc.)   Chengdu Anorectal Specialty Hospital is a tertiary first-class specialty hospital that integrates medical treatment, teaching, research, and preventive healthcare into a medical center. Its anorectal department is a nationally key clinical specialty, and the constipation department and pelvic floor center have a significant influence in the western region of China. The treatment for this clinical research will be conducted at the hospital's pelvic floor center.  Our team has accumulated certain clinical experience in the application effects and safety of peripheral magnetic stimulation in the treatment of CPPS. We have established standardized procedures for using transcranial magnetic stimulation to treat mental disorders such as anxiety and depression. According to relevant reports, the incidence of CPPS has shown an upward trend both domestically and internationally, and the presence of psychological issues is a major reason for its poor treatment outcomes. Therefore, it is particularly important to find effective treatment methods for CPPS patients with coexisting psychological disorders.  The research team currently has 5 senior technical staff members, 8 individuals with a master's degree or higher, and possesses rich experience in clinical research, patient follow-up, and statistical analysis. This ensures the accuracy of clinical data recording and statistical analysis. The talent structure is reasonable, with clear division of labor, which guarantees the smooth completion of this project. |

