3.3 Exit Standards

Participants will be asked to withdraw from the RCT under the following circumstances:

(1) If the patient does not adhere to the prescribed treatment plan or receives alternative treatment;

(2) If the patient experiences severe adverse reactions or changes in their condition that prevent them from continuing to participate in the trial;

(3) If the patient experiences significant organ dysfunction, unstable blood pressure, abnormal heart rate, or difficulty breathing;

(4) If the patient requests to withdraw informed consent due to intolerable adverse reactions or for no specific reason;

(5) If the patient loses follow-up during treatment or follow-up.

4. Plan Design

This study employs a prospective, randomized, blind, controlled trial design.

5. Sample Size Estimation and Grouping

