8.3 Safety Indicators

Blood routine, liver and kidney function tests, and electrocardiogram: Check whether the examination and treatment measures have caused harm to the participants.

9. Safety Evaluation:

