(5) Institutional Guarantees: Establish and improve the quality assurance system; ensure the qualifications of principal investigators; guarantee the facilities of various specialized departments; ensure the quality of clinical trial protocols; control the quality of clinical trial data; establish work systems, design specifications, and standard operating procedures that comply with GCP management regulations. Develop emergency plans for subject harm and unexpected events: establish a handling team for subject harm and unexpected events to ensure that subjects or patients receive timely treatment in the event of harm or unexpected incidents during the medical process; prepare and coordinate the prevention of subject harm and unexpected events, on-site control, emergency response, and other resources and technical support.

9.3.4 Adverse Events:

Adverse events (AEs) refer to any factors and incidents that may affect a patient's treatment outcomes, increase the patient's suffering and burden, potentially lead to medical disputes or accidents, and impact the normal operation of medical work and the personal safety of medical staff during clinical diagnosis and treatment activities as well as hospital operations. These events do not necessarily have a causal relationship with the treatment. Therefore, adverse events can be any negative and unexpected signs (including abnormal laboratory findings) and symptoms, or diseases that are temporally related to the use of medical products, regardless of whether they are considered related to the study.

During the research process, disease progression or deterioration (including increased pain and exacerbation of mental health issues due to disease progression) should be considered part of the efficacy evaluation and should not be reported as adverse events or serious adverse events.

During the clinical research period, all adverse events that occur will be reported on the adverse event page of the Case Report Form (CRF). The severity of adverse events will be classified using the "Classification and Grading Standards for Adverse Events in Medical Quality Safety" established according to China's "Medical Quality Management Measures" (https://www.gov.cn/zhengce) and will be reported in detail as required on the CRF.

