9.3.4.4 Adverse Event Handling Measures

(1) Take necessary treatment measures based on specific circumstances and decide whether to terminate the clinical trial. Detailed records of the symptoms, signs, or laboratory test results, including the time of occurrence, duration, severity, management measures, and progress, should be documented in the medical record. The researcher should evaluate the relevance to the clinical trial, sign, and date the record.

(2) When adverse events are discovered, researchers should immediately address the situation and report it to the project leader, the ethics committee, and the clinical research center. They should determine the necessary diagnostic and treatment measures based on the patient's condition and decide whether to terminate the clinical trial. All adverse events should be investigated and tracked, with detailed records of the handling process and outcomes maintained until the issue is properly resolved or the patient's condition stabilizes. If there are abnormal test results, they should be monitored until they return to normal. The method of follow-up can be chosen based on the severity of the adverse reaction, including hospitalization, outpatient visits, home visits, phone calls, or correspondence.

(3) Reporting of Adverse Events: During the study period, regardless of the treatment received by the patient, any serious adverse events or serious laboratory test result abnormalities that occur must be documented by the investigator on an adverse event report form and reported to the project leader, ethics committee, and clinical research center within 24 hours of becoming aware of them.

SAE report contact person: [name](Chengdu Anorectal Hospital Pelvic Floor Center)

Contact person: [name](Academic Committee of Chengdu Anorectal Hospital)

Mobile phone：[name]

Email：[contact]

Address: [name].

(4) Recording: Researchers should document the subjects' symptoms, signs, laboratory tests, the time of onset of damage, duration, severity, treatment measures, and progress in the original medical records and CRF forms, ensuring that the records are true, accurate, complete, timely, and legal. They should fill out the serious adverse event report form, sign it, and indicate the date; the original records should include the time, reporting method, and the reporting institution.

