(5) Follow-up: Researchers should follow up on all adverse events experienced by the subjects, determining the follow-up time based on the condition. During the follow-up process, necessary interventions and treatments should be provided to ensure that the harm to the subjects is minimized and to fully guarantee their safety. Detailed records of the follow-up process and the outcomes of the interventions should be maintained.

9.3.5 Emergency Response Measures:

(1) Measures for handling public health emergencies:

Report: During normal working days, on-duty medical staff should immediately report any incidents of harm to subjects to the incident handling team. On holidays or at night, they should report immediately to the administrative duty officer, who will then report to the subject harm and incident handling team. The team members should conduct a comprehensive assessment, make a preliminary judgment on the nature of the public health emergency, and report to the higher administrative department, suggesting whether to activate the emergency response plan for public health incidents.

(2) Activate the emergency plan: After approval from the higher health administrative department, activate the emergency plan for public health emergencies, including:

★ Establish special outpatient services, emergency services, and observation rooms.

★ Hospital leadership duty: The hospital office quickly formulated a duty schedule for the hospital leaders, ensuring that one leader is on duty 24 hours a day, fully responsible for emergencies; the medical department has dedicated personnel on duty 24 hours a day; all relevant personnel have their mobile phones on 24 hours a day to ensure smooth communication. Every morning at 8:00 AM and every afternoon at 5:00 PM, gather relevant information at the department, hold a focused discussion, and address related issues.

★ Ensure Material Supply: Urgently mobilize personnel, reserve relevant materials, transportation tools, as well as related facilities and equipment, to ensure the reasonable allocation of medical resources and guarantee the supply of emergency medical materials for key departments.

★ Evacuation or Isolation: Evacuate and isolate personnel as necessary based on the condition.

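### The laboratory and ECG safety tests have one post-baseline time point, after session 20, and none for patients who stop earlier

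*Protocol*

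**What the plan says.** Section 8.3 of the Protocol makes blood count, liver and kidney function and ECG the safety indicators, with this purpose: "Check whether the examination and treatment measures have caused harm to the participants". The Plan Summary lists the same tests and no others. The note to Table 1 in Appendix 2 shows where they sit in the schedule: "Routine examinations include: complete blood count, liver function, kidney function, and electrocardiogram examination". That row is ticked at t0 and t4 only, and the note defines the second point as "t4,At the end of 20 sessions".

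The Features and Innovations part of the project application announces a comparison of these indicators between arms: "By comparing the clinical safety and efficacy indicators among the three groups of patients".

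Section 3.3 lists the reasons for withdrawal, one of them being "If the patient experiences severe adverse reactions or changes in their condition that prevent them from continuing to participate in the trial". It attaches no examination to leaving.

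The adverse-event text is broad. Section 9.3.4 counts as adverse events "any negative and unexpected signs (including abnormal laboratory findings) and symptoms". Section 9.3.4.4 adds "All adverse events should be investigated and tracked" and "Researchers should follow up on all adverse events experienced by the subjects".

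**The concern.** A patient who stops before session 20 never reaches t4 as defined, and t4 carries the only post-baseline safety panel. Two of the withdrawal reasons in Section 3.3, severe adverse reactions and organ dysfunction or abnormal heart rate, are close to what the panel measures. The early stoppers may therefore differ from those who complete the course.

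At stake is the between-arm comparison of these tests. Section 11.2.1 places everyone enrolled and treated in the intention-to-treat population, so early stoppers belong to it, yet they have no planned value to contribute. No later analysis can recover a blood sample or ECG that was not taken when sessions stopped. For that reason the matter belongs in the protocol's visit schedule and cannot be left to the analysis plan.

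**Working it through.** **Step 1. Is a panel scheduled anywhere for an early stopper?**

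| Place in the Protocol | What it provides | Post-baseline panel for an early stopper? |
| --- | --- | --- |
| Appendix 2, Table 1 | Safety tests at t0 and t4; t1, t2, t3 and t5 blank; no early-stopping column | No |
| Section 3.3 | Withdrawal reasons only | No |
| Section 7 | Symptom, mood and quality-of-life scales, surface EMG, evoked potentials | No |
| Sections 9.3.4 and 9.3.4.4 | Work-up and follow-up when an adverse event or abnormal result exists | For cause only |
| Section 10.5 | Unspecified examinations 8 weeks after the course | Not named; Table 1 leaves the row blank at t5 |

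Table 1 also lists an analysis of missing items and non-respondents at t5. It can describe missing panels but cannot supply them. The Appendix 1 chart is not reproduced in the text reviewed, so anything it says about withdrawals is unknown.

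**Step 2. How exposed is this row compared with the others?** Post-baseline ticks in Table 1:

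- Safety tests: 1 (t4).
- Pelvic pain scale/NIH-CPSI, DASS-21, SF-36, surface EMG and evoked potentials: 5 each (t1 to t5).

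A patient who stops after session 5 has reached t1 and so has at least one scheduled value on every efficacy measure, but none on the safety tests.

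**Step 3. How many patients?** Section 5.1 gives 22 per arm, 66 in total and 10% dropout.

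- 0.10 × 66 = 6.6 patients overall.
- 0.10 × 22 = 2.2 per arm.

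The protocol does not split this dropout between the treatment weeks and the 8-week follow-up. I therefore assume that 0 to 2 of 22 per arm stop before session 20. That is 0 to 2/22 = 9.1% per arm, or 0 to 3 × 2 = 6 of 66 overall, and it leaves 20 to 22 per arm with a second panel.

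**Step 4. What precision is lost?** If none of n tested patients has an abnormal panel, the exact one-sided 95% upper bound on the abnormality rate is 1 − 0.05^(1/n).

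- n = 22: 1 − 0.05^(1/22) = 12.7%.
- n = 21: 1 − 0.05^(1/21) = 13.3%.
- n = 20: 1 − 0.05^(1/20) = 13.9%.

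The largest change within the assumed range is 13.9 − 12.7 = 1.2 percentage points.

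A harsher case uses the 54 patients that the sample-size calculation requires. 54/3 = 18 per arm, that is 22 − 18 = 4 losses per arm, all before session 20. The bound is then 1 − 0.05^(1/18) = 15.3%, a change of 15.3 − 12.7 = 2.6 points.

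These bounds measure precision only. They say nothing about bias from the missing patients being different, and the documents give no basis for its direction or size.

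**The case against.** The strongest reply is that a before-and-after panel is an ordinary design, nothing in the protocol contradicts it, and the patients who matter most for safety are already covered. Those leaving under 3.3(2) or (3) will usually have an adverse event. Abnormal laboratory findings count as such, all events must be investigated and followed, and serious laboratory abnormalities must be reported within 24 hours. This stands as far as detecting harm goes, and the point here does not claim otherwise. It does not supply a standard panel in all three arms, because for-cause testing depends on what prompted it.

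A second reply is that the remedy reaches few people. Patients who withdraw consent or are lost under 3.3(4) and (5) will mostly stay missing, and a panel after session 3 reflects a different exposure from one after session 20. Both statements are true. They limit the gain but do not remove it, and recording the number of sessions makes the difference in exposure visible.

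Third, the planned comparison appears only in general terms in the project application, without tests, time points or a method, and Section 11.2 names no laboratory analysis. That is fair. Section 8.3 nevertheless gives these tests the purpose of showing whether treatment did harm, which needs a value after treatment.

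Fourth, a patient who stops before session 5 has not reached a scheduled post-baseline point on any row. Also true: the contrast with the efficacy rows applies from t1 onwards.

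**Conclusion.** The point holds on the text available. The safety tests have a single post-baseline time point, tied to completing 20 sessions, and no provision is made for anyone who stops before it. For these tests the comparison between arms would rest on completers plus ad hoc results.

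The consequence is minor. With no early stoppers there is no gap. None of the named expected events in Section 9.3.4.3 is a blood-count, liver or kidney signal, so a decisive laboratory finding is not anticipated. The figures rest on an assumed timing of dropout and on Appendix 1 containing no exit assessment. The change is worth making because it costs little and the value cannot be obtained afterwards. It does not imply that safety monitoring in the trial is deficient.

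**What to change.** In Table 1 of Appendix 2, change the second tick for routine examinations from t4 to t4 or the day sessions are stopped, whichever is first. Apply this in all three arms, where the patient agrees, and record with the panel how many sessions the patient received.

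The cost is one table cell and one recorded number per patient. Nobody has an additional panel, since the planned second one is brought forward for early stoppers. The price is that exposure and the interval between panels will vary among early stoppers, so their results should be read with the session count beside them.

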(6) End of stimulation: The stimulation coil will be moved away from the patient's stimulation site. The patient will be informed that the treatment is complete, and the evaluator will ask if there is any discomfort. If the patient is lying down, they will be instructed to gradually sit up and then stand to avoid falling.

(7) Treatment process: Once a day, 5 days a week, for a total of 4 weeks (20 sessions). The treatment course ends after the 20th session.

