6.5 Treatment Plan

A treatment course will consist of 20 sessions, with five sessions per week, one session each day. The completion of the 20th treatment will mark the end of the course. Follow-up will be scheduled 8 weeks after the end of the course. During the study, patients may receive oral medication, and the specific medication and dosage must be recorded at the time of enrollment. If there are any significant adjustments to the type and dosage of the medication, they need to actively inform the therapist.

7. Follow-up Plan

(1) Assessment, follow-up plan and content: Patients need to return to the hospital for evaluation before treatment, at the end of each weekly treatment, and 8 weeks after the treatment course ends. The assessment includes the patient's pelvic pain score/NIH-CPSI, DASS-21 scale, SF-36 scoring scale, pelvic floor surface electromyography, and pudendal nerve motor evoked potentials.

(2) Establish a complete database and implement a follow-up mechanism managed by dedicated personnel.

(3) Follow-up time points: Before treatment, at the end of each weekly treatment, and up to 8 weeks after the end of the treatment course.

(4) Outside of the time points for in-hospital assessments and follow-up visits, dedicated follow-up medical staff will conduct tracking follow-ups through phone calls, written questionnaires, emails, and other forms.

8. Evaluation Indicators for Research Results

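### The schedule runs on two visit clocks, sessions completed and calendar weeks, which agree only with full attendance and leave early stoppers without a clear date for later visits

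*Protocol*

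**What the plan says.** **Session clock.** The note under Table 1 in Appendix 2 defines the first two on-treatment visits as "t1, At the end of 5 sessions;t2,At the end of 10 sessions" and the remaining visits as "t3,At the end of 15 sessions; t4,At the end of 20 sessions; t5, Follow-up visit 8 weeks after treatment ends".

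**Week clock.** Section 7(1) asks patients to return before treatment, then "at the end of each weekly treatment, and 8 weeks after the treatment course ends". Section 7(3) gives the time points as "Before treatment, at the end of each weekly treatment, and up to 8 weeks after the end of the treatment course". The columns of Table 1 are likewise labelled by treatment week, first to fourth.

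**End of the course.** Section 6.1(7) plans five sessions a week for four weeks and adds: "The treatment course ends after the 20th session". Section 6.5 repeats this, "The completion of the 20th treatment will mark the end of the course", and continues: "Follow-up will be scheduled 8 weeks after the end of the course". Section 10.5 ends participation eight weeks after the course.

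**Who is analysed and who leaves.** Section 11.2.1 places every patient who was enrolled and treated in the intention-to-treat population. Section 3.3(1) asks a patient who does not keep to the treatment plan to withdraw from the trial.

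The protocol does not date a visit from randomisation or first treatment, give a visit window, or state whether missed sessions are made up. It does not say when a patient who stops before session 20 is assessed.

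**The concern.** An outcome schedule should tell staff when to assess a patient whatever happens to treatment. Here the session clock makes later assessments depend on treatment received, and the week clock says something different as soon as one session is missed.

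Two things are at stake. First, outcomes for patients who stop early. They belong to the intention-to-treat population, but the schedule gives no settled date on which to measure them at the end of treatment or at follow-up. Section 11.2.2 plans repeated measures ANOVA, which in its usual form uses only patients with every time point. The routine blood tests and ECG have t4 as their only scheduled post-baseline visit, so those are affected too, although adverse events are followed separately.

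Second, comparability of timing. The pelvic pain score, NIH-CPSI and DASS-21 all ask about the past week, so a shift of seven days replaces the whole recall period. Stopping and missing sessions could differ by arm: section 9.3.4.3 lists local pain, headache and hearing changes as expected events, while the sham coil produces no field. The protocol gives no data on whether they do differ.

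**Working it through.** **Inputs.** Five sessions a week for four weeks (6.1(7)); t1 to t4 at 5, 10, 15 and 20 sessions and t5 eight weeks after treatment ends (Appendix 2 note); end of course at session 20 (6.1(7), 6.5).

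**1. The plan's own figure.** 5 × 4 = 20 sessions, which reproduces. With full attendance, t4 falls at the end of week 4 and t5 at week 4 + 8 = 12. For this patient the two clocks agree.

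**2. A patient who stops at session 12.** t1 (5) and t2 (10) have been reached. t3 (15) and t4 (20) are not reached under the session clock. Under 6.1(7) and 6.5 the course ends only at session 20, so t5 has no clear anchor. That leaves 3 of 5 post-baseline visits without a settled date. Under the week wording the same patient might be assessed at the end of weeks 3 and 4, but the text does not say whether a week without sessions counts.

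**3. A patient who misses sessions.** Assumptions: weekday sessions only, a Monday start as day 1, and missed sessions made up at the end. The nth weekday slot falls on day 7 × floor((n − 1)/5) + ((n − 1) mod 5) + 1. With m missed sessions, session 20 uses slot 20 + m, and t5 is 56 days later.

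| Missed and made up | t4 (day) | t5 (day) | Shift (days) |
|---|---|---|---|
| 0 | 26 | 82 | 0 |
| 1 | 29 | 85 | 3 |
| 3 | 31 | 87 | 5 |
| 5 | 33 | 89 | 7 |
| 10 | 40 | 96 | 14 |

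The first missed session costs three days because it pushes session 20 over a weekend.

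**4. The two clocks side by side.** A patient attending four sessions a week reaches session 20 after 20 / 4 = 5 weeks. The Appendix 2 note puts t4 at the end of week 5; section 7 puts the fourth assessment at the end of week 4, after 4 × 4 = 16 sessions.

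**5. If sessions are not made up.** Session 20 never occurs. There is then no delay; t4 and the t5 that hangs on it are simply undated under the session clock.

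**The case against.** The session counts may merely restate the planned regimen, with the week wording governing in practice. That is a fair reading, and it is why one should not infer that every visit is tied to completed sessions. Likewise, the t5 note taken alone could mean eight weeks after the last session actually given. Sections 6.1(7) and 6.5 cut against that, so the text is unsettled rather than plainly one thing or the other.

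The strongest objection concerns cause. Under 3.3(1), and 3.3(2) or (4) where they apply, a patient who stops at session 12 may already be out of the trial, whatever the visit clock says. This stands: the exit rule is probably the larger source of lost early-stopper data, and redating visits alone would recover little. The dating gap still remains for any stopper who is retained.

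Late assessment depends on make-up sessions that the protocol does not provide for. Treatment is at one centre, with one researcher assessing outcomes, so staff working to different clocks is not something the documents show.

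A reader might go on to infer a bias of stated size. Suppose 4 of 22 patients in an arm stop with no improvement and the other 18 improve by 0.8 SD. The completer mean exceeds the all-patient mean by 0.8 × 4/22 = 0.15 SD; with 2 to 6 stoppers the excess is 0.07 to 0.22 SD. These are assumed within-arm figures under a completer-only analysis. They do not measure bias in the comparison between arms: equal stopping with equal effects would create no spurious difference, and section 11.2 names an intention-to-treat analysis alongside per-protocol.

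Finally, assessing after a full course and eight weeks beyond it is a legitimate aim. It does not remove the need to say what happens when the course is not completed.

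**Conclusion.** The point holds as an inconsistency in visit dating that should be put right. The Appendix 2 note and the week wording of section 7 and the table diverge once a session is missed. Read with 6.1(7) and 6.5, they leave a patient who stops early without a clearly defined date for the remaining on-treatment visits and the 8-week visit, while 11.2.1 counts that patient in the intention-to-treat population.

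The size that can be derived is a timing shift of about 3 days for one missed session and 7 days for five, conditional on sessions being made up. For a stop at session 12, it is 3 of 5 post-baseline visits without a settled date. The documents support neither a figure for between-arm bias nor a claim that timing differs by arm. Loss of early-stopper data cannot be attributed to the visit clock alone, because exit rule 3.3(1) contributes and probably contributes more.

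**What to change.** In the Appendix 2 note and section 7, date t1 to t5 from the first session: end of weeks 1, 2, 3 and 4, and week 12. Use the same dates in all arms and hold the visits whatever number of sessions was received. Record sessions received to date at each visit as a separate variable. For a patient who has stopped sessions and will not attend, collect the pelvic pain score or NIH-CPSI and the DASS-21 on those dates through the telephone or questionnaire contact already provided in section 7(4), and record the mode.

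Sections 3.3(1) and 11.2.1 must be reconciled at the same time, so that stopping sessions does not by itself end outcome assessment for a patient who still consents. Without this the redating achieves little. The change concerns assessment dates only and takes no position on whether missed sessions are made up.

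**Cost.** Wording changes and one recorded variable, with no added planned visits. A patient with missed sessions is assessed at week 4 before session 20. Where sessions are made up, the week-12 visit falls less than eight weeks after the last one: with five made up, day 82 − day 33 = 49 days, or seven weeks. Some questionnaires will be collected remotely.
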